## Abstract

**Background:**

Everybody has the right to decide whether to receive specific medical treatment or not and to provide their free, prior and informed consent to do so. As dementia progresses, people with Alzheimer’s dementia (PwAD) can lose their capacity to provide informed consent to complex medical treatment. When the capacity to consent is lost, the autonomy of the affected person can only be guaranteed when an interpretable and valid advance directive exists. Advance directives are not yet common in Germany, and their validity is often questionable. Once the dementia diagnosis has been made, it is assumed to be too late to write an advance directive. One approach used to support the completion of advance directives is ‘Respecting Choices’^®^—an internationally recognised, evidence-based model of Advance Care Planning (ACP), which, until now, has not been evaluated for the target group of PwAD. This study’s aims include (a) to investigate the proportion of valid advance directives in a memory clinic population of persons with suspected AD, (b) to determine the predictors of valid advance directives, and (c) to examine whether the offer of ACP can increase the proportion of valid advance directives in PwAD.

**Method:**

We intend to recruit at least *N* = 250 participants from two memory clinics in 50 consecutive weeks. Of these, the first 25 weeks constitute the baseline phase (no offer of ACP), the following 25 weeks constitute the intervention phase (offer of ACP). The existence and validity of an advance directive will be assessed twice (before and after the memory clinic appointment). Moreover, potential predictors of valid advance directives are assessed.

**Discussion:**

The results of this study will enhance the development of consent procedures for advance directives of PwAD based on the ACP/Respecting Choices (R) approach. Therefore, this project contributes towards increasing the autonomy and inclusion of PwAD and the widespread acceptance of valid advance directives in PwAD.

*Trial Registration* DRKS, DRKS00026691, registered 15th of October 2021, https://www.drks.de/drks_web/navigate.do?navigationId=trial.HTML&TRIAL_ID=DRKS00026691

## Background

The right to make autonomous decisions is enshrined in law. Individual autonomy encompasses self-determined decision-making in medical contexts. PwAD have (like every other person) the right to decide whether to receive a specific medical treatment or not and to provide their free, prior, and informed consent to this treatment. To make treatment decisions, PwAD need to participate in an informed consent process, which requires that: (1) a competent person, (2) makes a free choice, and (3) following adequate information disclosure [1]. However, as dementia progresses, PwAD can lose their capacity to provide informed consent to complex medical treatment because of deterioration in cognitive function.

Despite such loss of capacity to consent, the availability of an interpretable and valid advance directive, an instrument to express the will of the affected person, can be considered to preserve their autonomy [2, 3]. To ensure the validity of an advance directive, its preparation presupposes informed consent that fulfils the above-mentioned three criteria. Important elements of informed consent are comprehension of one’s diagnosis, the progress of the illness and existing treatment options, and existing options at the end of life [4].

The use of advance directives is still not sufficiently widespread in Germany (approx. 51% of people above 60 years, [5]), and the interpretability and validity of those that do exist are questionable in about 50% of cases (e.g., regarding the question: Was the person capable of consent when preparing the advance directive?) [6]. The proportion of questionable cases is presumed higher in PwAD. Once the dementia diagnosis has been made, it is assumed to be too late to prepare an advance directive because the capacity to complete an advance directive (legal term: the capacity to consent) is considered questionable even when dementia is mild. In an older study, only one-fifth of those with early dementia (mostly of higher average premorbid intelligence) were considered competent to complete an advance directive [7].

The UN Convention on the Rights of Persons with Disabilities (UN-CRPD, ratified by Germany in 2009) is a human rights treaty that grants persons with disabilities, such as PwAD, the freedom to make their own choices (UN-CRPD, Article 3(1)). Therefore, according to the law, PwAD are considered as persons with valid legal capacity (UN-CRPD, Article 12). State parties are obliged to support their ability to make legally valid decisions.

One approach used to support the completion of advance directives is ‘Respecting Choices’®—an internationally recognised, evidence-based model of ACP, which, until now, has not been evaluated for the target group of PwAD. In Germany, according to § 43 Social Security Code XI, financing for ACP is only available to people living in nursing homes. Comparable services do not yet exist for those that have not been institutionalised.

### Study aims, research questions & hypotheses

The study’s aims include (a) to investigate the proportion of valid advance directives in a memory clinic population of suspected PwAD, (b) to determine the predictors of valid advance directives, and (c) to examine whether the offer of ACP can increase the proportion of valid advance directives in PwAD.

This study consists of two parts:

In part 1, we assess the status quo of advance directives in memory clinics. Part 1 is descriptive and explorative and uses an observational single-group design to answer the following research questions:What is the proportion of patients with (valid) advance directives in the population of memory clinic patients?How satisfied are memory clinic patients with their advance directives?Do demographic variables (age, gender, education, health literacy, need for autonomy, comorbidities, and/or dementia status) predict the existence and validity of advance directives?Study part 2 investigates the effects of offering ACP to memory clinic patients and is conceived as a non-randomized comparative trial with a baseline and an intervention phase. It is assumed that the offer of ACP is superior to no intervention (“care as usual”). The following hypotheses are investigated:When offered to take part in ACP (the intervention phase of the study), the proportion of patients with (valid) advance directives will be significantly higher than in the preceding baseline phase without the offer of ACP.When offered to take part in ACP (intervention phase of the study), the satisfaction of patients with their advance directives will be significantly higher than in the preceding baseline phase without the offer of ACP.

This study is a part of the comprehensive research project DECIDE (*Deci*sion-making places in Alzheimer’s *de*mentia—supporting advance decision-making by improving person-environment fit). DECIDE aims to enable PwAD benefit from their right to self-determination as much as possible.

## Methods

### Settings and participants

Participants will be recruited from two outpatient memory clinics (University Hospital Frankfurt, Germany; Kreisklinikum Siegen, Germany). We plan to recruit at least *n* = 125 participants at each location, with a total of *N* = 250 participants. This will be a convenience sample: Each patient presenting in either of the two clinics during the data assessment period (25 weeks for baseline and intervention phase, respectively) will be asked for participation as long as the inclusion criteria are fulfilled.

Patients are eligible for participation in the study if they present with suspected (mild or moderate) dementia. Since the capacity to consent to study participation could be an issue, the inclusion process will be based on the decision tree for the inclusion of non-consenting individuals in medical research [8]. Also, this allows us to include participants with questionable capacity to consent.

Exclusion criteria for study part 1 (status quo) are lack of capacity to consent to medical research with simultaneous incapacity for supported decision making by a relative or proxy or the lack of participant’s assent.

Exclusion criteria for study part 2 (intervention: ACP offer) are a final diagnosis of severe dementia by clinical rating, delirium, intellectual disability, severe mental illness, lack of capacity to consent to medical research with simultaneous incapacity for supported decision making by a relative or proxy, no assent by the patient, uncompensated pronounced sensory deficits, or insufficient knowledge of the German language, which makes the understanding of the study documents and/or the interview impossible.

In both study parts, there are no restrictions regarding concomitant interventions. Simulations were performed to determine the power of the analysis for our principal hypothesis: The proportion of valid advance directives increases when patients are offered ACP. Assuming that the proportion of valid advance directives during the baseline phase is 25% and can increase to 50% by offering of ACP and that an average of five patients are included weekly, the power is approximately 95%. We are positive to reach this number of participants; nonetheless, the sample size is constrained by the capabilities of the two participating outpatient memory clinics.

### Study design, intervention, and outcomes

In study part 1 (status quo), the overall sample is used in an observational cross-sectional single-group design. Outcomes are (1) the presence of an advance directive and its validity, (2) the patients’ satisfaction with this advance directive regardless of its validity, all assessed when patients present at the memory clinic for the first time.

In addition to this descriptive part, potential predictors of the presence of a (valid) advance directive are investigated. Variables of interest are demographic variables (e.g., age, gender, education), health literacy, need for autonomy in medical decision-making, cognitive status measured by the Mini-Mental State Examination (MMSE), mental health determined by the Geriatric Depression Scale (GDS), and physical and mental health status measured by the Somatic Morbidity Index (SMI) or the mental health score, respectively, of the Cumulative Illness Rating Scale—Geriatric (CIRS-G).

Study part 2 (intervention) uses a two-sample design with a blockwise allocation to baseline and intervention group. Hence, there is a baseline phase of 25 weeks, during which none of the participants receives ACP, and an intervention phase of 25 weeks, during which every participant receives ACP.

The intervention is the *offer* of an ACP (no: baseline phase/yes: intervention phase), but not the ACP process itself. The offer is made by the treating physician at the memory clinic, who also performs the informed consent procedure and collects the data.

The outcomes in this study part are the same as in study part 1: (1) the presence of an advance directive and its validity, and (2) the patients’ satisfaction with the existing advance directive (valid or not); always referring to the participant’s latest advance directive.

### Procedure

#### Data collection

The procedure is presented in Fig. 1. Data for study part 1 (status quo) is assessed at T0 and T1, data for study part 2 is assessed at T2.

**Fig. 1 Fig1:**
[figure not shown]
Procedure

In both memory clinics, participants with suspected dementia usually undergo three appointments: A medical history interview with the treating physician, a neuropsychological assessment, and an appointment for communicating the diagnosis. Moreover, the memory clinics try to follow-up on every patient, but this has not yet been performed reliably.

The study’s T1 incorporates the three appointments at the memory clinic. At the medical history interview (first appointment), participants consent to the present study (for details regarding informed consent, see below). Moreover, additional person-related variables not collected as part of the standard medical treatment will also be assessed, such as education, need for autonomy in medical decision making, health literacy, and comorbidities.

During the neuropsychological assessment (second appointment), the MMSE score is determined as a marker of cognitive decline and the score of the GDS [9] as a marker of depressive symptoms.

After communication of the diagnosis (third appointment), eligible participants in the intervention phase^1^ are asked whether they want to participate in ACP with the aim of creating an advance directive. If they consent, the study physician will arrange additional appointments besides the usual treatment to perform the ACP.^2^ The number and duration of these vary according to need. If not, a short questionnaire is filled out on the patient’s reasons for rejection.

Participants in the baseline phase^3^ do not receive the offer of ACP and are only contacted at follow-up (T2). For ethical reasons, they will be offered participation in ACP within the next 6 months after their appointments at the clinic (outside the present study).

As a consequence of this study, routine follow-up appointments via phone calls will be established as part of the memory clinic treatment. The primary aim of these follow-ups is to check if patients adhere to their medication or non-medical treatment and are able to handle any upcoming side effects. Moreover, questions from the patients or their caregivers about the diagnosis can be answered through these follow-up calls. For reasons of standardization, these follow-ups (T2) happen three to four weeks after a patient’s last appointment at the clinic.

The T2 questionnaire of this study records participation, outcome, and, if applicable, reasons for rejection, cancellation, or discontinuation of ACP (see Table 1). Participants will again be handed the advance directive questionnaire (see above). Participants who have not completed the ACP process at the time of the follow-up assessment will refer to a (possible) pre-existing advance directive (see statistical evaluation regarding sensitivity analyses on this topic). In addition, demographic data and the severity of dementia will be recorded. The study physician fills in all the answers known to him from the patient file or the ACP process to minimise the burden on the participants. If participants are not available on the phone at the agreed-upon time, the study physician will call them two more times before considering them lost to T2.

**Table 1 Tab1:** Participation in ACP yes/no, reasons and consequences

Participation in ACP	Reason/result
No,	… because he/she was not offered ACP (*baseline phase*)
	… because he/she declined the offer of ACP
Yes,	… the full ACP process has been performed
	… but the ACP process has not been completed yet
	… but the he/she has cancelled/discontinued the process
	… but it turned out during the ACP process that the patient was unable to consent
Other	(please describe)

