#### Primary outcome advance directive: existence and validity

Information on the existence and validity of the advance directive is collected at T0 in a self-report questionnaire and at T2 in a telephone interview. The closed questions were specifically composed for this study.

First, the existence of an advance directive is recorded (“Do you have an advance directive? Yes/no). This question acts as a filter: If no advance directive is available, none of the subsequent questions follows. If the answer is yes, the validity of the advance directive is assessed.

Since advance directives are highly-sensitive personal data, determining their validity via their content is ethically problematic in our view. One approach, therefore, is to ask whether informed consent was given by the participant when the declaration was drawn up, meaning (1) a patient capable of giving consent, (2) had received adequate information to make an informed decision, and (3) this decision had been voluntary [10]. The respective questions with dichotomous response options (yes/no, supplemented by “don’t know”), can be found in Table 2.

**Table 2 Tab2:** Questions on the validity of the advance directive

	Question
Prerequisite	Has the advance directive been made with a notary, physician or psychotherapist?
Adequate information	Has there been a medical/psychotherapeutic consultation?
	Has there been a notarial consultation?
Capacity to consent	Has your capacity to consent been documented by the physician/psychotherapist or the notary when the advance directive was drawn up?
Voluntariness	Did you create the advance directive voluntarily?

Besides asking about participants’ advance directive, in this questionnaire, we also ask about the existence of a guardianship, a guardianship directive, or a lasting power of attorney.

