#### Missing data

Missingness of data might be a concern in research question 3 of study part 1 (the association between person-related variables and existence and validity of advance directives) and in study part 2 (comparison of the frequency of advance directives, valid advance directives, and of the patients’ satisfaction with their existing advance directives during the baseline vs. the intervention phase). In study part 2 (intervention study), we assume that most missing data is created by participants accidentally skipping a question. Therefore, the study person receiving the questionnaires from participants goes through them and asks participants to fill in any missing data. In order to avoid a loss to follow-up, we designed the study follow-up as a low-threshold telephone interview with the additional motivating element that patients can use as a means to contact their treating physician to ask questions concerning their therapy. Therefore, we assume that all missing data will be lost completely at random in the intervention study and that the amount of missing data will be very low so we can obtain unbiased test results from a complete case analysis. In study part 1, however, more missings can be expected because a wider range of participants takes part in the study, particularly those with pronounced deficits that impair answering the questionnaire items. To ensure the best possible data quality, information may be provided by relatives or proxies (e.g., the existence and validity of advance directive). However, this does not apply to questions regarding the participant’s personal opinion (e.g., satisfaction with the advance directive, health literacy, autonomy in medical decision-making). Assuming that cognitive impairment is primarily responsible for the missingness of these data, we include the MMSE score in our model as a mediator variable. Therefore, we expect to obtain unbiased regressors even if the data are only missing at random and not missing completely at random.

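### The physician may fill in T2 validity answers from the ACP process, a source that only the intervention phase has, so the confirmatory outcome is ascertained unequally between phases

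*Protocol article*

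**What the plan says.** The section on the primary outcome collects existence and validity of the directive "at T0 in a self-report questionnaire and at T2 in a telephone interview". Validity is not judged from the directive's content. It is built from closed items about how the directive came about, answered yes, no or don't know. One of them is: "Has your capacity to consent been documented by the physician/psychotherapist or the notary when the advance directive was drawn up".

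The data-collection procedure adds a second route at T2: "The study physician fills in all the answers known to him from the patient file or the ACP process". The stated reason is to spare participants effort. For those who accept ACP, "the study physician will arrange additional appointments besides the usual treatment to perform the ACP". On roles, the design section says: "The offer is made by the treating physician at the memory clinic, who also performs the informed consent procedure and collects the data". Appendix B gives masking as none.

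Baseline-phase participants are not offered ACP within the study and are contacted only at T2. Intervention-phase participants who decline ACP stay in their group. Those with unfinished ACP at T2 answer about any directive they already had.

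The missing-data section says that "information may be provided by relatives or proxies (e.g., the existence and validity of advance directive"; this follows a passage on study part 1. For part 2 it assumes little missing data, missing completely at random, and a complete-case analysis.

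**The concern.** The two phases do not have the same sources for the same items. A baseline-phase participant with a properly made directive must, unless the file already holds the answer, remember on the telephone whether a professional was consulted and whether capacity was documented. In the intervention phase, a participant with an equally good directive who has entered ACP can have those answers supplied by a physician who learned them there. A no or don't know through forgetting is then possible in one phase and avoided for part of the other.

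This does not require a new directive. Someone whose ACP is unfinished is scored on an older directive, and its details may have come up in the ACP sessions.

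The affected outcome is the proportion with a valid directive, the only hypothesis reserved for confirmatory testing. The phases are sequential and not randomised, so like-for-like measurement matters all the more. The article describes no correction by source. The one named sensitivity analysis concerns incomplete ACP. The data management committee checks data entry, missing values and plausibility, not how the outcome was obtained. Paper records are destroyed after entry, so an unrecorded source cannot be recovered later.

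**Working it through.** **Inputs from the article.** Planned rates are 25% and 50% valid. Five patients per week over 25 weeks per phase gives 5 × 25 = 125 per phase. The test is a chi-squared test of two independent samples. Alpha and sidedness are not stated; two-sided 0.05 is assumed.

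**The plan's own figure.** The stated power is about 95%. Simulating weekly proportions (Poisson accrual, mean 5 per week) gives 95.4% with a Wilcoxon test and 94.6% with a t-test. The patient-level chi-squared test gives 98.6%. Nothing below depends on this figure.

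**Assumptions the documents do not supply.**
- p = 25% truly valid in both phases, so no true effect.
- r = share of holders of a valid directive who fail to confirm at least one item when interviewed.
- f = share of intervention-phase holders of a valid directive whose answers come from the physician, who is taken to be always right.
- No false yes answers.

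**Formulae.** Observed baseline rate = p(1 − r). Observed intervention rate = p[f + (1 − f)(1 − r)]. Spurious difference = p × r × f.

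Example with r = 0.20 and f = 0.5: baseline 0.25 × 0.80 = 20.0%; intervention 0.25 × (0.5 + 0.5 × 0.80) = 22.5%; difference 0.25 × 0.20 × 0.5 = 2.5 points.

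**Rejection probability**, summed exactly over the two binomial distributions (125 per phase, uncorrected chi-squared, two-sided 0.05):

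| Recall failure r | Physician-answered share f | Observed rates | Difference, points | P(reject) |
|---|---|---|---|---|
| 20% | 0.25 | 20.0% vs 21.25% | 1.25 | 5.5% |
| 20% | 0.5 | 20.0% vs 22.5% | 2.5 | 7.5% |
| 20% | 1 | 20.0% vs 25.0% | 5.0 | 15.4% |
| 40% | 0.25 | 15.0% vs 17.5% | 2.5 | 8.0% |
| 40% | 0.5 | 15.0% vs 20.0% | 5.0 | 17.6% |
| 40% | 1 | 15.0% vs 25.0% | 10.0 | 50.5% |

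With the same source and accuracy in both phases (25% vs 25%) the test rejects in about 5%, as it should.

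**A second route: generous rating by an unmasked physician.** Suppose the physician answers for half of all intervention-phase participants and rates a share g of directive states that are not valid as valid. The observed intervention rate is 0.25 + 0.5 × 0.75 × g. For g = 10% it is 28.75% and the test rejects in 10.2%; for g = 20% it is 32.5% and 25.7%. The baseline rate is 25% in both.

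**Scale.** At an observed baseline of 20% to 25%, a difference of about 11 to 12 points is needed for significance. The largest spurious difference in the table is 10 points, against a planned 25.

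**The case against.** A reader might infer that this rule could manufacture the whole effect. The documents do not support that, for three reasons.

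- The physician has ACP-derived knowledge only of people who enter ACP. Decliners remain in the analysis and are interviewed as in the baseline phase. Table 3 lists already having a satisfactory directive as a reason to decline, so existing holders may well be among them. Rows with f = 1 are an extreme, not an expectation.
- What ACP mainly tells the physician about is a directive made in ACP. The outcome refers to the latest directive, so such a yes may correctly record a real effect. The bias is confined to unequal confirmation of equally valid directives and to unmasked judgement.
- The spurious differences above stay well short of 25 points.

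A reader might also infer that baseline answers rest wholly on impaired recall. That goes too far. The patient file serves both phases, not everyone with suspected dementia will have it, and nothing bars proxies at T2, although they are mentioned only in the context of part 1. Timing, telephone mode and call-back rule are common to both phases. How don't-know answers are scored may properly be left to an analysis plan and is not a fault of the article.

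All of this stands and limits the size. It does not remove the asymmetry: the article itself admits an information source that one phase lacks, in the hands of an unmasked data collector, without recording where each answer came from.

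**Conclusion.** The point holds as an unequal ascertainment of the confirmatory outcome. It favours ACP and affects the part of the intervention phase that enters ACP. It rests on a rule the article states, not on a detail left out.

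Its size cannot be fixed, because neither recall accuracy nor the physician-answered share is given. With physician entries for half of the intervention-phase holders, the false-positive rate is 7.5% at 20% recall failure and 17.6% at 40%. It would be close to nominal if self-report is accurate or few existing holders enter ACP. Where the asymmetry operates, it inflates both the type I error and the effect estimate. On its own it is unlikely to account for a difference of the planned size.

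**What to change.** Amend the T2 paragraph of the data-collection procedure:

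1. Ask every validity item of every participant, or of a proxy on the same terms in both phases, with one T2 script.
2. Record answers from the physician, the file or the ACP process in separate fields with a source flag, entered before the paper records are destroyed.
3. Apply one rule for don't-know answers in both phases.
4. Pre-specify the primary outcome analysis on participant or proxy answers alone, alongside the physician-supplemented version, and conclude in favour of ACP only if the two agree.

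Which version is primary is for the sponsor to decide. Recall-only answers could miss directives properly documented in ACP and so weaken a true effect; supplemented answers carry the asymmetry described here. Using the same script does not mask the interviewer, so some interviewer bias may remain.

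The cost is a revised form and script, a few more minutes per intervention-phase call and slightly more burden on participants. No new staff are needed.
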